### Data management and monitoring

The independent Data Monitoring Committee (DMC) of the Scientific Research Innovation Platform of the Seventh People’s Hospital of Shanghai University of Traditional Chinese Medicine will oversee project data administration, data analysis and monitoring. To endure privacy and reduce bias, the dataset will be stored, analysed, and archived pseudonymously.

### Safety and adverse events

The safety officer will record and report all study adverse events. The participant’s Informed Consent Form lists all study risks. All participants will complete a TMS/MRI adverse effects questionnaire after the session.

### Data analysis

This trial will implement intention-to-treat (ITT) analysis with statistical analysis by a non-evaluation and treatment researcher. Data will be documented in the CRFs. IBM SPSS will do statistical analysis (IBM Corp. Released 2013. IBM SPSS Statistics for Windows, Version 29.0. Armonk, NY: IBM Corp.). Continuous variables are presented as mean ± SD for normal distributions, or as median and inter-quartile ranges for non-normal distributions, whereas categorical variables will be reported as frequency. We will use Two-way analysis of variance with repeated measures for continuous variables that meet the requirements of a normal distribution and homogeneity of variance, or the Wilcoxon test if not. A chi-square test will be employed for categorical variables. Primary and secondary outcomes will be compared using the Pearson correlation coefficient. Data from repeated measurements will be analyzed using two-tailed multivariate analysis of variance. *p* values below 0.05 indicate statistical significance. If needed, Bonferroni correction will be used for multiple *post hoc* comparisons.

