**Methods:**

This will be an assessor and patients blinded, sham controlled and randomized controlled clinical trial involving a 4-week intervention and a 6-month follow-up. 117 people with FS will be equally allocated to the sham-rTMS + NMES group (Group A), low frequency (LF)-rTMS + NMES group (Group B) and high frequency (HF)-rTMS+ NMES group (Group C) through stratified randomization. Interventions will be provided in 5 sessions per week, with a total of 20 sessions. The primary outcome measurements will be the score of Constant-Murley. The secondary outcome measurements will include polysomnography, quality of life (QOL) by SF-36, muscle biomechanics by surface electromyography (sEMG), motor evoked potential (MEP), brain neuroplasticity by magnetic resonance imaging (MRI). Evaluations will be performed at six time points, including at baseline, 2 weeks and 4 weeks from the start of treatment, and 1 month, 3 months and 6 months following the end of treatment. Two-way analysis of variance with repeated measures will be applied to examine the main effects of the group, the time and group-time interaction effects for all outcomes.

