### Sample size calculation

The G*power software (version 3.1) was utilized to determine the minimal sample size necessary to identify a significant between-group difference in the present research. A systematic review and meta-analysis indicated that the pain and function are the primary outcome (32) with an effect size of 0.25 for CMS in detecting changes or improvements in pain and function scores in patients with FS (33). Based on a prior two-way repeated analysis of variance (ANOVA) F test, with a power of 0.80, an effect size of 0.25, three groups, six measurements, correlation among repeated measures of 0.5, and an alpha level of 0.05, 93 participants were required for this study. To account for a conservative drop-out rate of 20%, the final sample size will therefore be 39 participants in each group, for a total of 117 participants.

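### Intention-to-treat is promised, but the repeated-measures ANOVA and MANOVA named for the analysis, with no imputation stated, keep only patients with all six CMS values

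*Protocol article*

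**What the plan says.** Four statements in the protocol article bear on this.

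- **Population.** Data analysis: "This trial will implement intention-to-treat (ITT) analysis with statistical analysis by a non-evaluation and treatment researcher".
- **Model.** The same section: "We will use Two-way analysis of variance with repeated measures for continuous variables that meet the requirements of a normal distribution", with a Wilcoxon test as fallback. It adds: "Data from repeated measurements will be analyzed using two-tailed multivariate analysis of variance". On software: "IBM SPSS will do statistical analysis". The abstract names the same ANOVA for all outcomes: "Two-way analysis of variance with repeated measures will be applied to examine the main effects of the group, the time and group-time interaction" effects.
- **Visits.** Abstract: "Evaluations will be performed at six time points". Table 1 schedules the CMS at all six: baseline, weeks 2 and 4, and 1, 3 and 6 months after treatment. The Outcomes section places the primary endpoint at four weeks.
- **Expected loss.** Sample size calculation: "To account for a conservative drop-out rate of 20%, the final sample size will therefore be 39 participants in each group". This follows a requirement of 93 participants from a six-measurement repeated-measures ANOVA.

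The article gives no imputation step, mixed model or other rule for patients with a missing visit.

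**The concern.** Classical repeated-measures ANOVA and MANOVA take one row per patient with one column per visit, and a patient with any empty cell is deleted. This is a property of the methods; the article does not say it. With six CMS columns, the analysed set becomes the patients with six scores. The Wilcoxon fallback does not bring the others back.

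The consequence is sharpest at the primary time point. A patient assessed at week 4 who misses only the 6-month visit disappears from the week-4 comparison because of an event months later. The result would then be reported as intention-to-treat although it rests on completers.

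Comparing completers keeps the protection of randomisation only if, within each arm, completing follow-up is unrelated to outcome. The documents do not say who is likely to leave or whether the arms will differ, so bias is a risk here and not an established fact.

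**Working it through.** **Inputs from the document.** Three groups, six measurements, effect size f = 0.25, correlation 0.5, alpha 0.05, power 0.80, N = 93, drop-out 20%, final N = 117 (Sample size calculation).

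**1. The plan's own figures.** For the between-group test in a repeated-measures ANOVA, the noncentrality is λ = f² × N × m / (1 + (m − 1)ρ), with df = (k − 1, N − k).
- N = 93: λ = 0.0625 × 93 × 6 / 3.5 = 9.96, df = (2, 90), power 0.8001. The stated 93 reproduces.
- 93 / 0.8 = 116.25, rounded up to 117, or 39 per group. This also reproduces.

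The sample size arithmetic is correct and is not criticised here.

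**2. Who is left at the planned drop-out.** 117 × 0.80 = 93.6 patients with complete rows; 117 × 0.20 = 23.4 removed, about 8 per arm. Patients who leave before week 4 have no week-4 score to discard, so about 23 is a ceiling for discarded primary data.

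**3. Power of the planned test.**
- About 93 completers: 0.80, as planned.
- All 117 with no missing data: λ = 0.0625 × 117 × 6 / 3.5 = 12.54, power 0.889.

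A model using all observed data would lie between these values. Drop-out at the planned rate alone causes no shortfall against the target.

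**4. Single missed visits.** The rates here are assumptions; the documents give none. Each of the five follow-up visits is missed independently with probability p.

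| Drop-out | p | Complete fraction | Complete of 117 | Power, planned test |
|---|---|---|---|---|
| 0% | 5% | 0.95⁵ = 0.774 | about 91 | 0.79 |
| 20% | 2% | 0.8 × 0.98⁵ = 0.723 | about 85 | 0.76 |
| 20% | 5% | 0.8 × 0.95⁵ = 0.619 | about 72 | 0.68 |
| 20% | 10% | 0.8 × 0.90⁵ = 0.472 | about 55 | 0.55 |

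Even with no patient lost to follow-up, occasional missed visits use up almost the whole allowance.

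**5. Possible size of bias.** This is an illustration under assumptions not in the documents: no true difference, correlation 0.5 between visits, 20% loss after week 2 that depends on the week-2 score in one arm and is random in the others. In a simulation with logistic dependence of 0.5 or 1.0 log-odds per SD, the completers' week-4 mean in that arm shifts by about 0.05 or 0.09 SD. In the extreme case, where the worst fifth at week 2 leave, the shift is 0.5 × φ(−0.842) / 0.8 = 0.5 × 0.350 = 0.17 SD. The week-2 scores that drive the loss were observed, so a likelihood-based model that includes them can correct for it. A completers' analysis cannot.

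**The case against.** The strongest reply is that intention-to-treat and repeated-measures ANOVA conflict only if gaps are left unfilled. Imputing first would satisfy both statements, and a condensed article may leave that to an analysis plan that is not shown. This stands as a limit on wording. A reader might infer that the trial will certainly be a completers-only analysis; the documents support only that it is so as named, with no imputation stated. The reply does not remove the point, because the article fixes both a population and a method, and the method as written does not deliver the population.

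Three other stronger readings also fail.

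- **The sample size shows that drop-outs will be excluded.** It does not. Inflating 93 to 117 is routine under any later model, mixed models included.
- **A set number of week-4 scores will be thrown away.** The timing of drop-out is not given, so about 23 is only an upper bound.
- **The fix buys a large gain in week-4 power.** A baseline-adjusted week-4 comparison at f = 0.25 and correlation 0.5 has power 0.687 with 93 patients and 0.794 with 117. However, the plan does not name that test, and 117 assumes that every patient has a week-4 score. If half of those who leave do so before week 4 (an assumption, leaving about 105), the figure is 0.745.

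It is also fair to say that complete-case arm means stay unbiased when missingness depends on arm alone, so missing completely at random is a stricter condition than is needed.

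**Conclusion.** The point holds in this form: the stated population and the stated method do not agree once any visit is missed, and the article budgets for 20% drop-out. At that rate up to about 23 of 117 randomised patients leave the primary analysis, including any who were seen at week 4 and lost later. Power for the planned between-group test remains near 0.80, so the damage is possible bias, loss of the randomised set and wasted observed data. Power falls below target only if single missed visits are added, and those rates are assumed.

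The conclusion rests on two conditions: that the ANOVA and MANOVA are run in their classical complete-row form, and that no imputation step exists elsewhere.

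**What to change.** For CMS, replace the repeated-measures ANOVA and MANOVA with a likelihood-based linear mixed model for repeated measures. It should use every observed CMS value of every randomised patient, analysed as randomised. Keep baseline in the outcome vector, so that a patient with no follow-up score is not excluded and the set is intention-to-treat in fact. State the group contrasts at week 4 as primary.

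Multiple imputation before the named ANOVA is an acceptable alternative if the sponsor prefers to keep that model.

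Add one sensitivity analysis for data missing not at random, for example a delta shift applied to imputed week-4 values. Report the completers' analysis as supportive only.

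The mixed model is available in SPSS, the software already named, so the cost is revised wording and a little more analysis work. The Setting and recruitment section gives 1 September 2025 as the start of recruitment, so the change should be documented before unblinding.

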## Methods and analysis

### Study design

This will be an assessor and patients blinded, sham-controlled, randomized controlled clinical trial (RCT) involving a 4-week intervention and 6-month follow-up. A total of 117 patients with FS will be recruited and randomly assigned to the sham rTMS +NMES group (Group A), LF-rTMS+NMES group (Group B) and HF-rTMS+NMES group (Group C) at a ratio of 1:1:1. Figure 1 depicts a concise flowchart of the entire study, and Table 1 provides the schedule of events. The study protocol (2025-7th-HIRB-042) was approved by the Ethics Committee of the Seventh People’s Hospital of Shanghai University of Traditional Chinese Medicine and registered in the Chinese Clinical Trial Registry (ChiCTR2500098406).

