### Outcomes

Participants will be evaluated by physical therapists unaware of group assignments at various time intervals using the assessments detailed in Table 1. Furthermore, baseline age, gender, symptoms, duration, prior therapy, and frequently utilized medication will be documented via a questionnaire. The primary endpoint is the four-week duration, during which any side effects will be documented in real time.

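### The Wilcoxon fallback compares only two samples and cannot replace the three-arm, six-visit repeated-measures ANOVA, and the role of the added MANOVA is not stated

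*Protocol article*

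**What the plan says.** The Study design section sets three arms: "HF-rTMS+NMES group (Group C) at a ratio of 1:1:1". The abstract sets the visits: "Evaluations will be performed at six time points, including at baseline, 2 weeks and 4 weeks from the start of treatment", followed by three visits after treatment ends. It also names the outcome: "The primary outcome measurements will be the score of Constant-Murley". The Outcomes section places the primary endpoint in time: "The primary endpoint is the four-week duration".

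The abstract states the analysis for all outcomes: "Two-way analysis of variance with repeated measures will be applied to examine the main effects of the group, the time and group-time interaction effects". The Data analysis section repeats it, "We will use Two-way analysis of variance with repeated measures for continuous variables", but restricts it to variables "that meet the requirements of a normal distribution and homogeneity of variance, or the Wilcoxon test if not". Three sentences later the section adds: "Data from repeated measurements will be analyzed using two-tailed multivariate analysis of variance". It ends by offering Bonferroni correction for multiple post hoc comparisons, on condition that it is needed.

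**The concern.** A fallback has to answer the same question as the test it replaces. The question here is whether three arms differ, and whether they differ in their course over six visits. A two-sample rank test cannot answer that in one step. It has to be broken into pairwise comparisons or before-after comparisons, and the plan does not say which, at which visits, or at what significance level.

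The MANOVA sentence adds a second uncertainty. CMS, polysomnography, SF-36, sEMG and MEP are scheduled at all six time points and MRI at three, so every continuous outcome falls under both the ANOVA sentence and the MANOVA sentence. If the two results disagree, the text does not say which one the conclusion rests on. At stake are error control and the interpretability of any outcome that fails the assumption check, including the primary one if CMS fails it.

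**Working it through.** **1. The plan's own figure.** Inputs from the Sample size calculation section: effect size f = 0.25, k = 3 groups, m = 6 measurements, correlation ρ = 0.5, α = 0.05, power 0.80. For the between-group effect in a repeated-measures ANOVA:

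λ = N·f²·m / (1 + (m − 1)ρ) = 93 × 0.0625 × 6 / (1 + 5 × 0.5) = 34.875 / 3.5 = 9.96, with 2 and 90 degrees of freedom.

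Power is 0.8001, so N = 93 is reproduced. Dropout: 93 / (1 − 0.20) = 116.25, which rounds up to 117, or 39 per arm. The interaction version of the formula would give 24 and the time version 21. The stated number therefore belongs to the between-group effect of the repeated-measures ANOVA. It was not derived from a Wilcoxon test or a MANOVA.

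**2. What each test can deliver.**

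| Test | Compares | Three-group test | Time over six visits | Group-by-time |
|---|---|---|---|---|
| Two-way repeated-measures ANOVA | all arms, all visits | yes | yes | yes |
| Wilcoxon rank-sum | two independent groups | no | no | no |
| Wilcoxon signed-rank | two paired occasions | no | no | no |

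**3. Size of the problem if the fallback is run pairwise.** Three arms give 3 pairs per visit. Five post-baseline visits give 3 × 5 = 15 tests.

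- If the tests were independent: 1 − 0.95³ = 14.3% for three tests, and 1 − 0.95¹⁵ = 53.7% for fifteen.
- The tests are in fact correlated, so simulation is the better guide. Set-up: no true difference, normal data, 31 per arm (93 / 3), ρ = 0.5 between visits, each test at 0.05. Separate runs of 2,000, 3,000 and 6,000 replicates gave 11–12% for the three week-4 tests and 38–42% for all fifteen.
- With Bonferroni (0.05 / 3 = 0.0167 and 0.05 / 15 = 0.0033 per test) the figures fall to 3.8% and 3.4%.
- A single Kruskal-Wallis test across the three arms at week 4 held 4.4%.

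**4. The MANOVA sentence.** In a repeated-measures general linear model, the multivariate and univariate tests of time and of group-by-time share the same null hypothesis and differ in whether sphericity is assumed. If that is what is meant, the sentence describes a second set of output from one model. If a separate MANOVA is meant, it is a competing analysis. The text fits either reading, and describing the test as two-tailed does not help, because an omnibus multivariate test has no tails in that sense.

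**The case against.** The strongest reply is that a main analysis is named and is consistent. The abstract, the sample size and the first analysis sentence all point to two-way repeated-measures ANOVA, and 93 follows from it. A reader might infer that the plan fixes no valid analysis at all; the documents do not support that. This part of the reply stands.

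It is also fair that the MANOVA may be the multivariate output that SPSS, the named software, prints beside the univariate tests. A reader might infer that it necessarily tests a different hypothesis; for time and group-by-time that is not established. What remains is that the text does not say so and does not say which result decides.

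On error rates, the 38–42% assumes fifteen uncorrected tests, any of which counts as success. The endpoint is set at four weeks, and the Bonferroni condition can be read as applying whenever several comparisons are made. The inflation then comes from missing correction and not from the rank test itself. This too stands: the figure is an upper case and not what the plan prescribes.

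A reader might further infer that signed-rank tests would be significant within every arm, sham included. The documents give no expected within-arm change or standard deviation for CMS, so this cannot be claimed, and nothing says that within-arm tests are intended.

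Finally, the fallback matters only if assumptions are judged to fail, the statistician is to be blinded, and details of assumption checks can sit in an analysis plan. These points limit the consequence. They do not rescue a named test that does not fit the design.

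**Conclusion.** The point holds in a limited form. The stated fallback is wrong for this design: no Wilcoxon procedure yields the group, time or group-by-time tests that it is meant to replace. The MANOVA sentence is unclear in its role and ranking. The main analysis is usable, and the sample size is not affected.

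The size depends on use. Unadjusted pairwise rank-sum tests would carry a family-wise error of about 11–12% at week 4, or about 38–42% over all post-baseline visits; corrected tests would stay below 5%. These figures assume 31 completers per arm, normal data, a constant correlation of 0.5 between visits and no true effect. The documents do not show that the assumption check will fail for CMS. A score bounded at 0 and 100 makes failure possible but does not establish it.

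**What to change.** In the Data analysis section:

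- Replace the Wilcoxon fallback with a method suited to three arms and repeated visits. Either keep the same longitudinal model with bootstrap intervals or a pre-stated transformation, or use Kruskal-Wallis on week-4 change with Bonferroni-adjusted pairwise follow-up.
- Name the repeated-measures model as the governing analysis, with the between-group comparison at week 4 as primary, in line with the Outcomes section.
- Delete the MANOVA sentence, or state that it refers to the multivariate tests of that same model and is supportive.
- Make the Bonferroni correction for pairwise arm comparisons unconditional.

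Replacing the whole analysis with a different class of model is not required to cure this defect. The cost is wording only, and 93 and 117 stay as stated. Recruitment began on 1 September 2025, so the change should be dated and made before unblinding.

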Aim 1: To evaluate the efficacy of NMES combined with rTMS over the contralateral M1 area in reducing pain intensity and improving functional ability in patients with FS. And to compare the efficacy of LF-rTMS+NMES and HF-rTMS+NMES in patients with FS.

Aim 2: To investigate the correlation between the clinical efficacy and neuro-biomechanism of cortical alternation in patients with FS after conducting systematic evaluations both before and after treatment.

Aim 3: Based on this study protocol and its anticipated outcomes, clinicians can develop innovative management strategies for pain and motor function in patients with FS, aiming to achieve effective therapeutic results.

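### The only method named for Aim 2 is a plain Pearson correlation, which accounts for neither arm nor baseline although treatment is expected to move both shoulder function and cortical measures

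*Protocol article*

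**What the plan says.** Aim 2, in the Introduction, is "To investigate the correlation between the clinical efficacy and neuro-biomechanism of cortical alternation in patients with FS". The same sentence fixes the timing loosely, as "after conducting systematic evaluations both before and after treatment". Under Data analysis, one sentence serves this aim: "Primary and secondary outcomes will be compared using the Pearson correlation coefficient". The sentence names no visit, change score, arm term or baseline term. The sentence that follows, "Data from repeated measurements will be analyzed using two-tailed multivariate analysis of variance", is not tied to the correlation. The general threshold is "values below 0.05 indicate statistical significance".

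Table 1 schedules CMS, surface electromyography (sEMG) and motor evoked potential (MEP) at six visits, and MRI at three (baseline, week 4 and the 6-month follow-up). The headings under Outcomes place sEMG, MEP and MRI under neuro-biomechanism, and polysomnography and SF-36 under clinical effectiveness.

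The Introduction also says that high-frequency rTMS raises cortical excitability, that low-frequency rTMS lowers it, and that either may relieve pain.

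**The concern.** A Pearson coefficient across all randomised patients mixes two things: how the two measures move together among patients treated alike, and how far the arm means differ on both. If active rTMS improves CMS and also shifts a brain measure, the coefficient departs from zero even when, within every arm, a patient's brain change says nothing about that patient's recovery. If the two frequencies push a brain measure in opposite directions while both improve CMS, the arm differences add noise and weaken a real within-arm link.

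Baseline raises a related problem. Correlating post-treatment levels brings in stable differences between patients that have nothing to do with response to treatment.

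At stake is the mechanistic conclusion, which the article presents as one of the trial's strengths.

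**Working it through.** **Inputs from the Sample size calculation section.** "with a power of 0.80, an effect size of 0.25, three groups, six measurements", "correlation among repeated measures of 0.5", two-sided 0.05, 93 evaluable patients, 117 after 20% dropout. Allocation is 1:1:1 (Study design), so 31 evaluable per arm.

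**The plan's own figure.** For the between-groups test in a repeated-measures ANOVA, λ = f²·N·m / (1 + (m − 1)ρ) = 0.0625 × 93 × 6 / 3.5 = 9.96. With 2 and 90 degrees of freedom the power is 0.8001, and 93 / 0.80 = 116.25, rounded up to 117. Both figures reproduce. The article gives no figure for the correlation analysis.

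**Step 1: correlation created by arm alone, one row per patient.** Let both active arms shift by d SD from sham on both measures, with no link within arms.
- The SD of the three arm means is f = d√2/3. So d = 0.53 gives f = 0.25, and d = 1 gives f = 0.47.
- The pooled correlation is r = f² / (1 + f²): 0.0625/1.0625 = 0.059 for d = 0.53, and 0.2222/1.2222 = 0.182 for d = 1.
- With 93 pairs, |r| above 0.204 is significant. By Fisher's z, with standard error 1/√90, the rejection rates are about 8.6% and 41%.

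Simulation agrees:

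| Shift in both active arms, both measures | Mean r | Plain Pearson | Adjusted for arm |
|---|---|---|---|
| None | 0.00 | 5% | 5% |
| 0.53 SD (f = 0.25) | 0.06 | 8-9% | 5% |
| 1 SD (f = 0.47, assumed) | 0.18 | about 43% | 5% |

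**Step 2: do change scores cure it?** No. With ρ = 0.5 the SD of a change is √(2(1 − 0.5)) = 1 times the SD of a level, so f is the same. Simulated rates for unadjusted change scores are 8-9% at f = 0.25 and 42-43% at f = 0.47. Adjusting for arm, or for arm and both baselines, gives 4-6% in every scenario run.

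**Step 3: levels instead of changes.** Suppose stable differences between patients correlate 0.5 across the two measures (assumed) and ρ = 0.5. Post-treatment levels then correlate 0.5 × 0.5 = 0.25 although the changes correlate 0. By Fisher's z this is significant in about 68% of trials.

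**Step 4: opposite shifts.** Let CMS shift by (0, 0.53, 0.53) and MEP by (0, −1, +1) SD in sham, low- and high-frequency arms, with a true within-arm r of 0.3. The MEP shifts and the r are assumed.
- The between-arm covariance is (0 − 0.53 + 0.53)/3 − (mean CMS shift × 0) = 0.
- The total variances are 1 + 2(0.53²)/9 = 1.062 for CMS and 1 + 2/3 = 1.667 for MEP.
- The pooled r is 0.3/√(1.062 × 1.667) = 0.225.
- Power is about 59% with plain Pearson and 83% with arm adjustment, by Fisher's z and by simulation.

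**Step 5: only if visits were stacked as independent rows.** With no link, no arm effect and no trend, the variance of r is inflated by 1 + (m − 1)ρ². For m = 3 this is 1.5, and the false-positive rate is P(|Z| > 1.96/√1.5) = 11%. For m = 6 it is 2.25, giving P(|Z| > 1.96/1.5) = 19%. Simulation gives the same rates.

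**The case against.** The strongest reply is that the article is silent on these choices and does not choose badly. Pearson coefficients on change scores, at a single visit or within each arm would all fit the sentence; Aim 2's reference to evaluations before and after treatment points towards change; and a condensed article may leave visit and covariates to the full plan. Much of this stands. A reader might infer that the six CMS visits, or the three MRI visits, will be stacked as independent rows. The article does not say so. The rates in Step 5 therefore describe a possible misuse, and still higher rates would need an assumed common time trend as well. The lack of a rank-based alternative for the correlation is likewise only missing detail and no error.

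The reply does not remove the arm problem. The method that is named has no place for arm, and moving to change scores leaves the inflation as it was. Separate coefficients within each arm would avoid it, but nothing in the text asks for them.

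Two further points are fair. First, if treatment moves both measures, the pooled association is real; it is just not evidence that, among patients treated alike, more brain change goes with more recovery. To call it a link where none exists would overstate the matter. Second, equal and opposite MEP shifts in the two active arms, with equal CMS gains, create no spurious correlation, as the zero covariance in Step 4 shows. In that case the harm is lost power. The article gives no comparable direction for the MRI measures.

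**Conclusion.** The concern holds in limited form. The one method named for Aim 2 does not account for arm or baseline in a trial designed to move both sides of the correlation. With one row per patient the inflation is modest on the protocol's own effect size (5% to about 8-9%) and large only under an assumed 1 SD shift (about 43%). Both figures assume that the two active arms shift the same way on both measures, and even the lower one carries the CMS effect size over to a brain measure. Where the two frequencies act in opposite directions, the loss is in power: 59% against 83% in the example, with assumed shifts and an assumed r of 0.3.

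This is worth correcting because a better method is available from data already scheduled. It bears on the mechanistic aim only. The primary CMS comparison is untouched, and 93 and 117 reproduce.

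**What to change.** Replace the Pearson sentence, for Aim 2, with wording to this effect: the baseline-to-week-4 change in CMS will be related to the baseline-to-week-4 change in each neuro-biomechanism measure (sEMG, MEP, MRI), using one pair per participant and a partial correlation, or the equivalent regression, adjusted for arm and for the baseline values of both measures. Rows from different visits will not be stacked. Results will be labelled exploratory. The change from baseline to the 6-month follow-up may be analysed in the same way.

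The change is to wording only and needs no new data. It costs a few degrees of freedom and possibly less favourable p-values.

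### The pairwise arm comparisons get Bonferroni only at discretion and with no binding omnibus gate; a closed procedure on four-week CMS, or Holm, would fix the rule and save power

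*Protocol article*

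**What the plan says.** The Data analysis section sets one significance limit (p "values below 0.05 indicate statistical significance") and plans a two-way repeated-measures ANOVA, with a Wilcoxon test if its assumptions fail. On multiplicity it says: "If needed, Bonferroni correction will be used for multiple" post hoc comparisons. It gives no criterion for need, does not list the comparisons, and does not make them conditional on the ANOVA.

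Aim 1 in the Introduction asks whether rTMS added to NMES works, and continues: "And to compare the efficacy of LF-rTMS+NMES and HF-rTMS+NMES in patients with FS". All three pairs of arms are therefore of interest.

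The Sample size calculation section powers only the ANOVA F test, "with a power of 0.80, an effect size of 0.25, three groups, six measurements". The abstract describes the planned tests as group, time and group-by-time effects. The Outcomes section places the primary endpoint at four weeks.

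**The concern.** An omnibus F test does not say which arms differ, so the pairwise tests carry the trial's conclusions. The error rate for those tests depends on a judgement that can be made after the data are seen.

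Two things are at stake. Three pairs tested at 0.05 with neither a gate nor a correction exceed 5% family-wise error. Bonferroni at 0.05/3 = 0.0167 per pair is valid but stricter than three arms require. With exactly three arms, any two true pairwise null hypotheses imply that all three means are equal. An omnibus test at 0.05 followed by each pair at 0.05 is therefore a full closed procedure that holds 5%, provided the omnibus test and the pairs concern the same endpoint.

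**Working it through.** **Inputs from the Sample size calculation section.** f = 0.25, 3 groups, m = 6 measurements, "correlation among repeated measures of 0.5", alpha 0.05, power 0.80, 93 evaluable (31 per arm), 117 enrolled (39 per arm).

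**Assumption.** The article gives only f, not the three means. Two patterns were used:
- two arms alike: f = 0.471d, so d = 0.25/0.471 = 0.53 SD;
- evenly spaced: f = 0.408d, so the extreme pair differs by d = 0.25/0.408 = 0.61 SD.

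**1. The plan's own figure.** For the between-group test, lambda = f² × N × m / (1 + (m − 1) × rho) = 0.0625 × 93 × 6 / 3.5 = 9.964. With 2 and 90 df the power is 0.8001 (0.795 at N = 92). Then 93/0.8 = 116.25, which rounds up to 117. Both figures reproduce.

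**2. Family-wise error with all arms equal, 31 per arm, one contrast per pair.**

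| Rule | Error |
|---|---|
| Unadjusted, no gate | 12.1% (exact, studentized range) |
| Bonferroni | 4.3% |
| Closed (omnibus, then pairs at 0.05) | 5.0% |

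At 39 per arm the unadjusted figure is 12.2%. When one arm truly differs, the closed procedure rejects the remaining true null hypothesis 5.0% of the time.

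**3. Power for a truly different pair (simulation, pooled error).** For the six-visit mean, the SD is √(3.5/6) = 0.764 of the single-visit SD, so 0.53 becomes 0.694 and 0.612 becomes 0.802.

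| Setting | Pair | Bonferroni | Holm | Closed | Closed − Bonferroni |
|---|---|---|---|---|---|
| Six-visit mean, n = 31 | two alike | 61.6% | 65.0% | 72.2% | 10.6 |
| | even, adjacent | 20.0% | 25.6% | 33.7% | 13.7 |
| | even, extreme | 76.3% | 77.0% | 79.4% | 3.1 |
| Six-visit mean, n = 39 | two alike | 73.7% | 76.8% | 82.7% | 9.0 |
| | even, adjacent | 25.9% | 33.3% | 41.5% | 15.6 |
| | even, extreme | 86.5% | 86.9% | 88.5% | 2.0 |
| One visit, n = 31 | two alike | 36.8% | 39.2% | 46.1% | 9.3 |
| | even, adjacent | 11.3% | 14.1% | 20.2% | 8.9 |
| | even, extreme | 48.9% | 49.9% | 53.5% | 4.6 |
| One visit, n = 39 | two alike | 46.6% | 49.6% | 57.0% | 10.4 |
| | even, adjacent | 14.6% | 18.4% | 25.5% | 10.9 |
| | even, extreme | 60.8% | 61.7% | 64.9% | 4.1 |

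The closed procedure gains 9 to 11 points when two arms are alike, and 2 to 16 points over all rows. Holm gains about 1 to 6 points at 31 per arm; at 39 per arm the range is 0.4 to 7.4.

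**4. Does the gate have to be the same endpoint?** Setup: 31 per arm, six visits, correlation 0.5, all arms equal at week 4, one arm different only at the three follow-up visits. Week-4 pairs were each tested at 0.05.

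| Follow-up difference | Gate: six-visit group test | Gate: week-4 omnibus test |
|---|---|---|
| 0.53 SD | about 6% | 5% |
| 1.06 SD | about 9% | 5% |
| 2 SD | about 12% | 5% |

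The six-visit test can open the gate because of follow-up differences. The week-4 pairs are then unprotected.

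**The case against.** The strongest reply is that the 12% is not what the article describes. Post hoc comparisons ordinarily follow a significant ANOVA. With a gate on the same endpoint, dropping Bonferroni still gives 5%; with Bonferroni and no gate the error is 4.3%. A reader might infer that the plan runs at 12%. The document does not support that, since no sentence adopts the reading in which both safeguards are dropped. What stands is that the wording does not exclude it, and that the planned ANOVA spans six visits, so even an implied gate would not reliably protect four-week pairs.

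Second, Bonferroni is valid, comes with simultaneous confidence intervals, and still works under the Wilcoxon fallback, for which no three-arm omnibus test is stated. All of this is true. Naming Bonferroni is not an error; the case against it is only the avoidable loss of power.

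Third, a flat loss of 10 points would be an overstatement. It holds when two arms are alike, which is an assumption; for the extreme pair of evenly spaced arms the loss is only 2 to 5 points.

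Fourth, an analysis plan may settle the details. That would excuse silence, but the article does state a rule, and it makes that rule conditional on an undefined judgement.

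**Conclusion.** The point holds as a weakness in wording and a cheap improvement, of minor to moderate weight. The correction for the comparisons that answer Aim 1 is discretionary and no omnibus gate is binding. The 12% is the worst case the text allows, not its expected behaviour. Bonferroni controls the error but gives up about 9 to 11 points of power per true difference if two arms are alike, and about 2 to 16 points across the patterns and sample sizes examined.

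These figures assume one outcome, one contrast per pair, normal data with equal variances, and f = 0.25 applied either to one visit or to the six-visit mean. They do not cover multiplicity across visits or outcomes. A reader might also infer that the ANOVA already planned can serve as the gate. It cannot: its group and interaction tests run over six visits, while the primary endpoint is read here as week 4.

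**What to change.** Delete the conditional words and replace the sentence with, for example:

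*For CMS at four weeks, the three pairs (LF versus sham, HF versus sham, LF versus HF) are each tested at two-sided 0.05 only if a three-arm omnibus test of four-week CMS, in the same model, is significant at 0.05; otherwise no pair is declared significant. The six-visit group and group-by-time tests do not serve as this gate. Where no omnibus test of the same endpoint is used, including under the Wilcoxon fallback, the three pairs are tested by Holm's procedure.*

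Holm needs no gate and is never less powerful than Bonferroni. State separately how comparisons among time points and across outcomes are handled, because the three-arm shortcut does not extend to them.

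The cost is a few lines of text, fixed before unblinding, with no extra participants or assessments. The small downside is that the closed procedure has no matching simultaneous confidence intervals; ordinary 95% intervals would be reported beside the decisions.
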